## Introduction

1

Remimazolam, a benzodiazepine ultra-short-acting sedative, has been used in general anesthesia in Japan since August 2020; it was first implemented in Japan. This medication has similar characteristics as propofol (eg, it is short acting) and is expected to be used in a similar manner. Clinical trials conducted in Japan have reported that its effect on hemodynamics is less than that of propofol and is considered an easy-to-use sedative in patients with unstable circulation.^[1,2]^

Although anesthetics were originally designed to prevent intraoperative awakening, some surgeries (such as brain surgery under awake conditions) require awakening for medical reasons in the middle of the surgery.^[3]^ Traditionally, propofol has been used in such surgeries because it allows for rapid awakening. However, intraoperative awakening inevitably causes patients discomfort during surgery. If that memory persists postoperatively, it may have a traumatic effect on the patient.

Remimazolam has been used in surgeries that require awakening the patient in the mid-surgery because it allows for rapid awakening (similar to propofol and antagonists). Since remimazolam is a benzodiazepine, it is expected to cause anterograde amnesia (similar to other benzodiazepines)^[4,5]^ and to decrease the discomfort caused by intraoperative awakening; this property is expected to have a positive effect on preventing psychological trauma.

Clinically, we observed that patients have no memory of the immediate postoperative period after general anesthesia with remimazolam. In addition, based on postoperative interviews of patients sedated with remimazolam, we found that all patients had no memory of postoperative pupillometry examination, bed transfer, or conversations occurring during and shortly following sedation. However, we cannot conclude that remimazolam causes anterograde amnesia based on the current evidence because there is no established method to evaluate anterograde amnesia, and our observations are anecdotal and obtained within the scope of our practice. Specifically, this study aims to compare the effects of different sedatives used in general anesthesia on memory retention in postoperative patients and to establish a method to evaluate effects on anterograde amnesia in validation clinical trials.

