### Study design

2.2

The standard protocol items for randomized trials guidelines were followed. The present study is an exploratory, open, propofol-controlled, single-center, randomized controlled trial (RCT) to compare the efficacy and safety of remimazolam with propofol. The study will be conducted by the Department of Anesthesiology and Critical Care Medicine, Kyushu University Hospital. In total, 70 patients aged 20 to 65 years will be randomly assigned to receive remimazolam or propofol as sedative anesthetic agent. The participants will be randomly divided into 2 groups using stratified block randomization. The study design is summarized in Figure 1 and available at URL (https://upload.umin.ac.jp/cgi-open-bin/ctr_e/ctr_view.cgi?recptno=R000052026)).

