#### Primary endpoint

2.7.1

The primary endpoint to be examined in this RCT is the assessment of anterograde amnesia. This will be examined as the number of posters remembered among 4 posters 24 hours after surgery (see Figure S1, Supplemental Digital Content, which illustrates the pictures) shown after awakening from anesthesia. Specifically, after awakening from anesthesia and being able to say their names, patients are to be shown 4 posters.^[6]^

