#### Secondary endpoints

2.7.2

(1)Retrograde amnesia, based on the number of events remembered from prior to the start of anesthesia – ambulatory entry, bed transfer, vein insertion, BIS monitor attachment to the forehead, and mask fitting – and whether the patient remembers the poster (see Figure S2, Supplemental Digital Content, which illustrates the numeric characters) shown before the induction of anesthesia.(2)The dose of analgesic medication administered from the time the patient returns to the ward until 24 hours after surgery.(3)Immediate postoperative pain numerical rating scale (NRS) values (see Figure S3, Supplemental Digital Content, which illustrates the NRS).(4)Pain NRS scores 24 hours after leaving the operating room.

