### Data collection

2.9

Data will be recorded and stored via REDCap software (Nashville, TN) while the study is in progress, and the data will then be exported from the database into statistical software for analysis.^[7,8]^ REDCap, which allows for additional data privacy and security protections compared with other data storage platforms, has an audit trail that records every time a participant or staff member makes changes to any data entered on the website. The data used for this study, although not available in a public repository, will be made available in an anonymized and de-identified form to other researchers upon reasonable request. Data and outcome assessors are blinded.

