### Ethics approval and consent to participate

2.14

This trial is being conducted at Kyushu University in Japan. The study has received approval from the ethics review board at the Kyushu University School of Medicine Hospital Institutional Review Board (IRB approval number: 20212006) and will be conducted in accordance with the World Medical Association Declaration of Helsinki and its later amendments. All participants will be required to sign a written consent form prior to participation. Before consent is obtained, the investigators will provide an oral explanation of the study to each participant. Participation is voluntary, and patients’ privacy will be protected. The participants will be informed of their right to withdraw from this study at any time, and that this will not affect their clinical care. If this study poses a serious health risk to a participant, compensation will be provided. The study results will be published in a peer-reviewed journal and will be presented at national and international conferences.

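### The trial is open and only data and outcome assessors are listed as blinded, yet recall and pain come from the patient: the plan should keep patients unaware of their drug until the 24-hour assessments are recorded

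*Protocol article*

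**What the plan says.** Section 2.2 (Study design) sets the label: "The present study is an exploratory, open, propofol-controlled, single-center, randomized controlled trial (RCT". The abstract and the Discussion also call the trial open. The only statement of who is blinded closes section 2.9 (Data collection): "Data and outcome assessors are blinded". Patients are not named there.

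The outcomes that depend on the patient's own answer are:

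- the primary endpoint (2.7.1), "the number of posters remembered among 4 posters 24 hours after surgery"
- the first secondary endpoint (2.7.2), "Retrograde amnesia, based on the number of events remembered from prior to the start of anesthesia", together with recall of a poster shown before induction
- the third, "Immediate postoperative pain numerical rating scale (NRS) values"
- the fourth, "Pain NRS scores 24 hours after leaving the operating room"

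The Introduction says of remimazolam that "it is expected to cause anterograde amnesia". Section 2.14 adds: "Before consent is obtained, the investigators will provide an oral explanation of the study to each participant". Neither that section nor any other says whether a patient may learn which drug she was allocated before she is assessed.

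**The concern.** For these four endpoints the patient produces the result and the assessor writes it down. An assessor who does not know the arm cannot introduce bias of his or her own, but cannot remove bias that the patient brings. A patient who knows her drug can also unblind the assessor by mentioning it.

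A patient who has heard the study explained, and who knows she received the drug under suspicion of erasing memory, may search less hard or say sooner that she remembers nothing. Knowledge of the drug may also alter how she rates pain.

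The stakes come from the purpose of the study. Section 2.1 aims to establish a method for evaluating anterograde amnesia in later validation trials. Sections 2.10 and 2.12.1 say the results are meant to inform a confirmatory trial. A measurement procedure open to patient expectation would pass that weakness on, and an effect estimate distorted by it would mis-size the next trial.

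**Working it through.** **Who is protected, endpoint by endpoint**

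| Endpoint | Who supplies the result | Can it be checked? | How knowledge of the drug could act |
|---|---|---|---|
| Posters remembered, 0 to 4 (2.7.1) | Patient | Yes, against the posters shown | Effort or willingness to report; direction follows the expected amnesia |
| Retrograde events and pre-induction poster (2.7.2) | Patient | Partly | As above, between the other two in exposure |
| Immediate pain NRS (2.7.2) | Patient | No | Rating itself; no direction stated |
| Pain NRS at 24 hours (2.7.2) | Patient | No | Rating itself; no direction stated |

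The blinding in 2.9 acts on the recording step in every row and on the patient's answer in none.

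**Effect on planning the next trial.** For a fixed SD, error rate and power, the required sample size is proportional to 1/δ², where δ is the true difference. If expectation adds b in the same direction, the estimate carried forward is δ + b. The next trial would then be given a fraction (δ/(δ + b))² of the patients it needs. The document gives neither δ, b nor the SD, so no figure can be put in.

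**Illustration on the error rate.** The protocol has no figure to reproduce here, since 2.10 says that no sample size calculation was made (35 × 2 = 70 agrees with the stated total).

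Inputs from the document: 35 patients per group (2.10); two-sided level .1 (2.12.1), hence a critical value of 1.645. Assumed, not from the document: no true drug effect, and a shift of b SD caused by patients' knowledge of their drug.

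- Standard error of the mean difference = SD × √(2/35) = 0.239 SD
- P(significant) = Φ(b/0.239 − 1.645) + Φ(−b/0.239 − 1.645)

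| Assumed shift b | 35 per arm | 30 per arm (assumed per-protocol size) |
|---|---|---|
| 0 | 0.100 | 0.100 |
| 0.1 SD | 0.130 | 0.125 |
| 0.2 SD | 0.216 | 0.200 |
| 0.3 SD | 0.350 | 0.317 |

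The 30-per-arm column is shown because 2.12.1 analyses the per-protocol set, which may hold fewer than 35 per arm. The standard error there is SD × √(2/30) = 0.258 SD. Both columns use a normal approximation for what is, in the primary endpoint, a count from 0 to 4.

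**The case against.** The strongest reply has four parts.

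*Patients may already be unaware.* A reader might infer from the word open that patients are told their drug. The document does not say so. The label would also fit a trial in which only the anaesthesia team knows, and the consent form and full protocol are not shown. This stands as a limit: patients' knowledge is an inference. It does not remove the point, because the article does say who is blinded, patients are not among them, and nothing stops disclosure before the assessment. If patients are in fact kept unaware, the remedy is to write that down.

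*The primary endpoint is fairly objective.* Recall of specific posters can be checked, and expectation cannot create a memory that was never formed. This stands. It is wrong to treat poster recall as being as vulnerable as a pain score. A patient can still under-report or try less hard.

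*No direction is given for pain.* A reader might suppose that pain bias would also favour remimazolam. The Introduction states an expectation about amnesia only, so that is not supported.

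*No decision rests on a p-value.* Section 2.12.1 makes descriptive statistics the main analysis, with the covariance analysis as additional information. A reader might take the error rates above as the trial's real false-positive risk. They are not: the shift is assumed, and the study is exploratory. A biased estimate carried into later planning remains a concern.

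An open design with blinded assessors is also a legitimate, disclosed choice, and the protocol does not contradict itself. Here, though, the choice leaves the patient-supplied outcomes unprotected when the gap could be narrowed cheaply.

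**Conclusion.** The concern holds in a limited form. As written, the plan blinds those who record and handle the outcomes and is silent on the patient who supplies them, so poster recall, retrograde recall and both pain scores are left open to expectation. Pain is the most exposed; poster recall is less exposed, with a likely direction towards the hypothesis.

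The main consequence is a possibly biased estimate and a measurement method that hands the same weakness to the confirmatory trial. The size is unknown. The range of about 13% to 35% for the nominal 10% error rate rests wholly on an assumed shift of 0.1 to 0.3 SD, no true effect, 35 per arm and a normal approximation.

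This is a worthwhile and inexpensive improvement, not a flaw that invalidates the trial.

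**What to change.** 1. In 2.2, state: *open to the anaesthesia team; patients are not told their allocation until the 24-hour recall and NRS are recorded.*
2. In 2.9, keep the existing blinding of data and outcome assessors and add patients. Say that this covers the immediate NRS and the poster viewing as well as the 24-hour interview. Concealment therefore starts before induction. It ends only when both 24-hour assessments are done, because the recall is timed from surgery and the NRS from leaving the operating room.
3. Keep the syringe and infusion line out of the patient's view before loss of consciousness where practicable.
4. If a question about the guessed drug is added, also ask the reason for the guess and whether the patient saw or was told the drug. A guess made after the recall test partly reflects the drug's own effect: a patient who remembers nothing may name remimazolam for that reason. By itself it is not a clean measure of unblinding.

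**Cost.** A change to the consent wording with an ethics amendment and, if used, a few extra interview questions. Dose, sample size, endpoints and analysis do not change. Concealment will be imperfect. Section 3.1 says recruitment began on October 13, 2021, so a change now leaves participants under two conditions. Those enrolled before it must be identified in the report. If patients are already kept unaware, only the wording in 2.2 and 2.9 needs to change.

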### Sample size

2.10

Since this is an exploratory study, a sample size calculation was not performed. The researchers aimed for 70 participants because this was considered a feasible number for enrolment that will provide sufficient information for the confirmatory trial.

There have been no similar studies in the past, and we set the number of patients in each of the 2 groups to 35 cases each; we estimate that this number of patients can be enrolled within approximately 6 months.

### Adverse events

2.11

All adverse events (AEs) that occur between the day of surgery and the end of day 2 after surgery will be recorded. A serious AE is defined as any adverse reaction resulting in any of the following outcomes: a life-threatening condition, death, or a condition that requires inpatient hospitalization or prolongation of an existing hospitalization and threatens to cause disability. Any serious AE will be documented in the medical records and reported to the Clinical Research Board by the responsible investigator, in accordance with the Japanese governmental regulations. If necessary, the investigators will administer treatment for any AE occurring during the course of the study.

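### Section 2.11 defines a serious adverse event too narrowly: hospitalisation and disability are joined by 'and', and the definition starts from an 'adverse reaction'

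*Protocol article*

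**What the plan says.** Section 2.11 of the protocol article makes three statements that bear on this point.

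- Recording: "All adverse events (AEs) that occur between the day of surgery and the end of day 2 after surgery will be recorded". No cause is specified.
- Definition: "A serious AE is defined as any adverse reaction resulting in any of the following outcomes". The outcomes listed are a life-threatening condition, death, or "a condition that requires inpatient hospitalization or prolongation of an existing hospitalization and threatens to cause disability".
- Reporting: a serious event is entered in the medical records and "reported to the Clinical Research Board by the responsible investigator, in accordance with the Japanese governmental regulations".

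The article gives no other definition of a serious event and does not define 'adverse reaction'.

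**The concern.** Two features of the definition make it narrower than the section seems to intend.

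First, the third outcome ties hospitalisation or prolonged stay to a threat of disability with 'and'. Disability is never a criterion of its own, and prolongation does not suffice alone.

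Second, the base term changes from one sentence to the next. Recording covers adverse events; seriousness is defined for an adverse reaction. In ordinary usage a reaction implies a causal link to the drug, so the wording can be read as requiring a causality judgement before seriousness is considered.

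What is at stake is what the Clinical Research Board sees. Serious events are the only ones that section 2.11 says are reported to it, so the definition decides which events reach it.

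**Working it through.** No figure is involved, so the check is logical.

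**Step 1: the 'and'.** Let H be a new hospitalisation, P a prolonged stay and D a threat of disability. The third outcome can be grouped in two ways:

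- Reading A: (H or P) and D
- Reading B: H or (P and D)

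The last column shows the result if every item were joined by 'or'. All rows concern events that are neither fatal nor life-threatening and that pass the 'adverse reaction' condition.

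| Event | Reading A | Reading B | All joined by 'or' |
|---|---|---|---|
| P without D | not serious | not serious | serious |
| D without H or P | not serious | not serious | serious |
| H without D | not serious | serious | serious |
| P with D | serious | serious | serious |

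The first two rows fail under either grouping, so the gap does not depend on how the sentence is parsed. The third row differs between the groupings, so the sentence is also ambiguous about a new admission. Only death and a life-threatening condition clearly stand alone.

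**Step 2: the base term.** As worded, an event is serious if it is an adverse reaction and has a listed outcome. If the term means drug-related, any event judged unrelated fails the first condition, and even a death judged unrelated is not serious. If it is a loose synonym for adverse event, the condition excludes nothing. The article does not settle which is meant.

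**Step 3: is it corrected elsewhere?** Sections 2.6 (Discontinuation criteria), 2.7.3 (Safety endpoints), 2.12.2 (Safety analysis) and 2.13 (Monitoring) neither restate nor widen the definition. The reference to Japanese regulations in section 2.11 concerns how a serious event is documented and reported, not which events count as serious.

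**Step 4: what depends on it?**

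- Recording: unaffected, because it covers all adverse events.
- Reporting to the board: affected, because only serious events are named.
- Planned comparisons: unaffected. Section 2.12.2 compares hypotension, bradycardia, rhabdomyolysis and anaphylaxis whatever their seriousness, and section 2.7.3 has no serious-event rate among its endpoints.

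**Step 5: which route matters most here?** Patients return to a ward and are assessed there to 24 hours (sections 2.7.2 and 2.7.3), and events are recorded to the end of day 2. The article gives no length of stay. On the assumption that most patients are still in hospital during that window, prolongation is a more natural route to seriousness than a new admission, and it is the route that 'and' narrows under both readings.

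**The case against.** The strongest reply is that this is loose drafting in a condensed article. The 'and' may be a slip, or a translation of 'or'. 'Adverse reaction' appears in a section headed Adverse events, inside a sentence that defines a serious AE, so a synonym is at least as plausible as a deliberate causal restriction. The full protocol (version 1.0) and the regulations may contain the proper criteria, and neither is shown.

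Part of this stands. The exclusion of unrelated events is conditional on the usual meaning of an undefined term. The reply does not rescue the 'and': the article does not leave the definition to another document but states one, and the stated one fails under both groupings. If it is a slip, correcting it is all the easier to accept.

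A reader might also infer four stronger things that the article does not support.

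- *Events escape expedited reporting.* No expedited pathway or timeline is stated, only reporting to the board under national regulations.
- *The Safety Monitoring Committee is misinformed.* Section 2.6 lets that committee stop the trial, but nothing says it relies on these reports.
- *Under-reporting differs by arm because the trial is open.* No causality assessment is described, nor who would make it. Section 2.9 says data and outcome assessors are blinded, without saying whether this covers adverse events.
- *Safety rates shift by some percentage points with 35 patients per group.* No serious-event rate is compared, and any count of misclassified events would be invented.

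**Conclusion.** The definition in section 2.11 is wrong as written. Under either grouping, a prolonged stay without a threat of disability is not serious, nor is a disabling event without hospitalisation or prolongation, and neither need be reported to the Clinical Research Board. Both conclusions rest on the wording alone. The further conclusion, that events judged unrelated are left out, rests on the assumption that 'adverse reaction' means drug-related.

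The size is limited and cannot be put as a number from the article. Events that miss the definition remain on record as adverse events. The primary and secondary endpoints, the sample size, the significance level and the section 2.12.2 comparisons are untouched. What is weakened is the classification of serious events and the information that reaches the board. That is enough to justify a correction.

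**What to change.** Replace the definition in section 2.11 with one along these lines: a serious AE is any adverse event, whatever its cause, that results in death, is life-threatening, requires inpatient hospitalisation or prolongs an existing stay, or causes or threatens to cause disability. Join every item with 'or', use 'adverse event' throughout, and record the causality judgement as a separate item. If the full protocol already has such a definition, bring the article's wording into line with it.

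Section 3.1 says recruitment is under way, so events already on record should be re-read against the corrected wording. This is possible because all adverse events are recorded.

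The cost is one sentence and possibly a few more reports to the board. Treatment, sample size and analysis do not change.

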### Statistical considerations

2.12

The full analysis set is defined as all patients enrolled in this study, excluding cases of serious noncompliance with ethical guidelines for life sciences and medical research involving human subjects, untreated cases, and unobserved cases (ie, complete absence of the primary endpoint). The per-protocol set (PPS) is defined as the population of patients included in the full analysis set who do not meet any of the following conditions:

(1)Patients who do not meet the selection criteria specified in this protocol or who violate the exclusion criteria.(2)Significant deviations from the study protocol.(3)Patients who fail to receive sufficient anesthetics (ie, the BIS value during surgery not being lower than that before induction of anesthesia).(4)Cases of concomitant use of prohibited drugs.

The safety analysis set comprises the population of patients who receive at least 1 dose of the study drug.

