### Discontinuation criteria

2.6

For individual study participants:

If the principal investigator or sub-investigator determines that continuation of the study is not feasible for any of the reasons listed below, the patient will be removed from this study. In such cases, the reason for discontinuation will be explained to the patient as necessary.

(1)Study participants declining to participate in the study or withdrawing their consent.(2)The principal investigator or subcontractor deciding that it is appropriate to discontinue the study.(3)The entire study plan being canceled.

Discontinuation, suspension, or termination of the trial:

If the Safety Monitoring Committee decides to stop the trial, the entire trial will be stopped.

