#### Analysis of primary and secondary endpoints

2.12.1

Because the goal of this small exploratory study is to generate appropriately powered large-scale RCTs for future, we will perform descriptive statistics using PPS. After evaluation with descriptive statistics, for additional information, analysis of covariance including the baseline value as a covariate will be performed for comparison of groups. If the distribution is greatly skewed in a blinded review, transformation of values such as logarithmic transformation will be considered. As a sensitivity analysis of the primary endpoint, the same analyses will be performed for the PPS. All analyses will be performed with a two-sided significance level of .1.

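### A patient with no poster count is dropped from every primary and secondary analysis, including endpoints that do not depend on the post-awakening posters

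*Protocol article*

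**What the plan says.** Section 2.12 (Statistical considerations) takes enrolled patients as the FAS but removes, among others, "untreated cases, and unobserved cases (ie, complete absence of the primary endpoint"). It then nests the second set in the first: "The per-protocol set (PPS) is defined as the population of patients included in the full analysis set", less those who meet any of four further conditions.

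Section 2.12.1, which covers the primary and secondary endpoints together, states that "we will perform descriptive statistics using PPS". It adds: "As a sensitivity analysis of the primary endpoint, the same analyses will be performed for the PPS". No wider set is named for any efficacy endpoint.

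The primary endpoint is the number of posters, out of four, recalled 24 hours after surgery. Section 2.7.1 sets the condition for showing them: "after awakening from anesthesia and being able to say their names, patients are to be shown 4 posters". It gives no time limit, and no score for a patient who is never shown them.

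The secondary endpoints in section 2.7.2 are retrograde recall (events and a different poster, both from before induction), "The dose of analgesic medication administered from the time the patient returns to the ward until 24 hours after surgery", immediate pain NRS, and "Pain NRS scores 24 hours after leaving the operating room".

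The safety analysis set is everyone who received at least one dose of study drug.

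**The concern.** The rule makes the presence of one endpoint a condition for analysing all the others. A pain score or an analgesic dose has no statistical reason to depend on whether a poster count exists. Valid randomised data on the secondary endpoints would be set aside.

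For the primary endpoint, the selecting event comes after randomisation. Being shown the posters requires a level of recovery that the sedative can affect, and the protocol itself compares time to full awakening between arms. If untested patients differ from tested ones, or if their number differs by arm, the remaining patients are no longer the groups that were randomised.

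The trial is meant to establish a method of evaluating anterograde amnesia and to inform later, powered trials. How often the poster test cannot be completed in each arm, and why, is information those trials would need. The analysis sets as written do not bring it out.

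**Working it through.** **Inputs from the protocol article.** FAS and PPS definitions (2.12); set used for the endpoints (2.12.1); condition for showing the posters (2.7.1); list of secondary endpoints (2.7.2); 35 patients per arm (2.10). The protocol gives no recall mean, SD or missing rate. It states that no sample size calculation was done, so the only figure to reproduce is 35 + 35 = 70, which agrees.

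**Step 1: set membership.** No primary endpoint → not in the FAS → not in the PPS, which lies inside the FAS → in none of the primary or secondary analyses. Section 2.12.1 names the PPS for both the main and the sensitivity analysis. If one of these was meant to be the FAS, the result is unchanged, because the FAS already excludes the patient.

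**Step 2: which endpoints need the four post-awakening posters.**

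| Endpoint | Needs the posters? | Analysed if the count is absent? |
|---|---|---|
| Poster recall at 24 h | Yes | No |
| Retrograde recall | No | No |
| Analgesic dose to 24 h | No | No |
| Immediate pain NRS | No | No |
| Pain NRS at 24 h | No | No |
| Safety endpoints | No | Yes (safety set) |

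**Step 3: size for the primary endpoint (illustration).** Let k patients in one arm of 35 have no count and let the other 35 − k average m. Scores run from 0 to 4.

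- Lower bound of the arm mean: (35 − k)m/35. Upper bound: [(35 − k)m + 4k]/35. Width: 4k/35, whatever m is.
- Fall in the arm mean if the missing are scored 0: m − (35 − k)m/35 = km/35.

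With m = 1.5 assumed:

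| k (assumed) | Share of arm, k/35 | Width, 4k/35 | Fall if scored 0, 1.5k/35 |
|---|---|---|---|
| 1 | 2.9% | 0.11 | 0.04 |
| 2 | 5.7% | 0.23 | 0.09 |
| 3 | 8.6% | 0.34 | 0.13 |
| 5 | 14.3% | 0.57 | 0.21 |

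For k = 3, the lower bound is (32 × 1.5 + 3 × 0)/35 = 48/35 = 1.37 and the upper bound is (48 + 12)/35 = 60/35 = 1.71. Over m = 1 to 3 and k = 1 to 5, the fall when the missing are scored 0 runs from 1 × 1/35 = 0.03 to 5 × 3/35 = 0.43 posters.

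**Step 4: precision is not the issue.** With an assumed SD of 1.0, two-sided alpha 0.1 and 80% power, the detectable difference is (1.645 + 0.842) × √(1/35 + 1/35) = 0.594 for 35 against 35. It is (1.645 + 0.842) × √(1/35 + 1/30) = 0.619 for 35 against 30. The concern is selection after randomisation and discarded data.

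**The case against.** The strongest reply is that few patients, perhaps none, will be affected. The posters have no time limit, so a slow waker can be shown them later. The section on the investigational drug describes a reversal step. Entry is limited to patients under 65 without impaired cognition and below ASA class IV. A patient who sees the posters and recalls none scores 0 and stays in, so amnesia itself does not produce a missing value. All of this stands.

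It also rules out some stronger readings:

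- A reader might infer that the most sedated patients will vanish from the analysis. The documents name no such group. A missing count could equally come from a missed 24-hour interview or withdrawn consent.
- A reader might infer that the remimazolam effect is biased towards no difference. That needs an excess loss of heavily sedated patients in that arm, and nothing in the documents establishes one.
- A reader might set the 0.34 range (k = 3) against a 90% confidence half-width of about 0.52 (SD 1.3 assumed) and call it two-thirds. That compares a full range with a half-width. Against the full width of about 1.04 it is about one-third, and every input is assumed.
- Section 2.6 says of an investigator's decision to discontinue that "the patient will be removed from this study". A reader might add this as arm-aware selection in an open trial. It is not part of the FAS definition, and the article states that outcome assessors are blinded.

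Three further points can be made for the plan. Safety data are kept, including time to full awakening, so a difference in emergence would still be visible there. An FAS that requires some outcome data is common. Imputation detail usually belongs in the SAP. But the point does not rest on missing detail. It rests on a stated rule by which the absence of one endpoint removes the data for all the others, and no named analysis brings them back. The reason for the missing count also matters: a patient who misses the 24-hour interview may lack the 24-hour pain score as well, so the secondary data lost will vary from patient to patient.

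**Conclusion.** The point holds as a defect in the analysis-set definition. The loss of secondary data follows from sections 2.7.2, 2.12 and 2.12.1 alone and needs no assumption about sedation. For the primary endpoint the loss is potentially informative, because having a count depends on recovery after randomisation. Its frequency and direction cannot be known from the documents, and it may be nil.

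On assumed figures, one to three patients lost from an arm of 35 leave that arm's mean uncertain by 0.11 to 0.34 posters. If they are scored 0 and the rest average 1.5, the mean falls by 0.04 to 0.13. These are illustrations, not forecasts. The change is worth making because it is cheap and decides which data are analysed.

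**What to change.** - **FAS.** Define it as all randomised patients who received a study sedative, whether or not the primary endpoint is present. The PPS stays nested in it; state that a missing poster count is not in itself a reason for exclusion from the PPS.
- **Secondary endpoints.** Analyse each in all patients who have it.
- **Primary endpoint.** Report the number of missing poster counts, with reasons, by arm. Add a sensitivity analysis that sets missing scores to 0 and to 4 by arm.

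The cost is a wording change in the protocol and SAP, one extra table, and a slightly wider reported range if any counts are missing. If none are, the results do not change.
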